## Methods

### Study Design

The study used a quantitative longitudinal study design. It will be implemented in three phases: (1) the cocreation and adaptation of the intervention; (2) the baseline survey; and (3) follow-up surveys conducted at 1 month, mid-term follow-up at 3 months, and an endline at 6 months. The cocreation phase was completed during the recess term (July 2025). The next 2 phases, baseline and follow-ups, will be implemented between February 2026 and October 2026. Recruitment will begin in February 2026 and will last for 3 months up to April 2026. There will be an observation period of 6 months for the enrolled participants [28,33,43].

The email and WhatsApp messaging intervention was cocreated and adapted by the study team together with purposively selected students and identified stakeholders. Thereafter, a baseline survey will be conducted before recruitment to estimate the prevalence of SAD. Students at Makerere University will be invited via email and WhatsApp to self-subscribe to the W4S program. All participants who subscribe to the intervention will receive a link to the online baseline survey, daily supportive messages for 6 months, and the follow-up survey links at 1-, 3-, and 6-month postenrollment time points [33,43].

The rationale for the nonrandomized design is based on resource constraints. We have funding to implement a pilot survey and use the preliminary results to apply for a bigger grant to implement a fully randomized controlled trial.

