**Methods:**

This study has a quantitative longitudinal research design. We will target 4494 undergraduate students aged 18 to 24 years who will be recruited from Makerere University, Uganda. Through advertisements on social media platforms (WhatsApp and X [formerly known as Twitter]) and websites, students will receive a link to the W4S website with information about the intervention. Eligible students will voluntarily self-subscribe to the W4S program by providing their email addresses. The subscription will be an indicator of consent required for participation in receiving the intervention. Subscribers will receive daily supportive messages for 6 months. The data will be collected from subscribers at baseline (program initiation), 1 month, 3 months (midpoint), and 6 months (program completion) through web-based surveys. Students will complete questionnaires regarding SAD and well-being. We will conduct both descriptive and inferential statistical analyses using STATA version 17.

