### W4S Email and WhatsApp Messaging Intervention

The W4S program is a daily, supportive email and WhatsApp messaging intervention designed to mitigate symptoms of SAD and promote well-being. It is part of the broader ResilienceNHope suite, supported by a web-based platform and implemented through the Global Psychological eHealth Foundation. The initial content is developed by mental health professionals using CBT principles. Crucially, for this study, the program will be contextually adapted. The initial message database contains generic content that will serve only as a starting point for adaptation. Through participatory cocreation workshops with students at Makerere University, this content will be linguistically, culturally, and contextually adapted to ensure that metaphors, proverbs, and messages address specific contextual stressors for the students. This participatory process is central to the intervention’s design, ensuring it is not merely imported but is collaboratively shaped by its intended users [25,28,33,43].

Through a partnership with Makerere University, students will be able to self-enroll online. Upon registration, they will receive daily supportive, noninteractive (one-way) messages for 6 months, with the nature of the service clearly explained at the outset. Each day’s email and WhatsApp message will be unique, drawn from a large message database.

Examples of messages (not yet adapted) to be delivered to subscribers of the W4S email and WhatsApp messaging program include the following:

What you do today will determine how you are tomorrow. Rise up and take advantage of whatever opportunities today presents, and success will be yours tomorrow.There are 2 days in the week we should not worry about, yesterday and tomorrow. That leaves today, live for today.There are no surprises in store. You are in charge of the successes that await you. There may be some challenges, but you have the power to overcome them.

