### Data Collection

An online baseline survey will be conducted to assess the mental health of the students.

A link to the baseline survey will be sent to the students through their email and WhatsApp. Clicking on the link to the baseline survey will indicate consent required for participation in the survey. The data collection portal is secure and password-protected with dual authentication, which minimizes data breaches. In addition to the demographic questions, participants will fill out the online screening tools for assessing SAD and well-being. It is on this basis that they will be diagnosed (to have or not to have) with at least one of the 3 outcomes [8,48-50]. The app is programmed to produce summaries of the total number of subscribers at any given point in time and how many have completed the different phases.

All participants will be able to view their scores for each mental health outcome (SAD). Depending on the severity of the mental health scores, recommendations will be provided to participants. All students, whether diagnosed with SAD or not, will have the option to enroll in the W4S program and will be made available through a postbaseline subscription link. The baseline survey and intervention enrollment will be conducted from March 2026 to cover the second semester of the academic year 2025/2026 at Makerere University.

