### Participants’ Recruitment and Subscription

This study will be conducted among Makerere University students in Kampala, Uganda. We will consider currently enrolled students from year 1 to year 3 of study. We have made an assumption that all university students own smartphones based on a previous study [55]. Internet access is always guaranteed to all university students during the semester when the study will be implemented. We will broadcast information about the study through social media platforms used by university students, including WhatsApp, emails, and Twitter (subsequently rebranded X). We will also share information about the study through posters and by word-of-mouth within accessible groups. We will also engage the staff of the Counselling and Guidance Center at the University Hospital to inform students about this study.

During the broadcast, students will be informed about the possibility of being enrolled in a digital intervention program (W4S program). The study will be launched through an announcement by the office of the Dean of Students of Makerere University, the Students’ Guild, and the Director of Makerere University Hospital. All interested students will be provided with a link to the W4S website to self-subscribe to the study. Potential respondents will be asked to register for the study with their active emails and also consent to being part of the study. Once they have electronically consented to the study, they will receive another link to the baseline study. The cocreated and adapted messages will be sent to subscribers’ email and WhatsApp daily at 7 AM East African Time. Each subscriber will receive the W4S program daily for 6 months.

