### Sample Size Estimation

The total student population at Makerere University, Kampala, Uganda, is about 35,000 [41]. It is estimated that the sample size needed for our prevalence estimates with an expected SAD prevalence of 50% [10,12], a 95% interval, and a 2% margin of error for moderate-to-high stress, moderate-to-high anxiety, and moderate-to-high depression among Makerere University students will be 2247. A sample size calculator was used to determine the sample size [28,59,60].

Based on the previous maximum survey completion rates of 50% observed in similar programs, a minimum of 4494 students will be enrolled in the W4S email and WhatsApp messaging program over 6 months to obtain an estimated 2247 students’ completion at baseline. To achieve a power of 80% (*β*=.2) and a 2-sided significance level of 5% (*α*<.05) and to detect an effect size of 30% before and after the intervention, a sample size of 90 would be needed [49].

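### The protocol gives two incompatible orders for survey, subscription and messages; under one, baselines can follow exposure and prevalence is measured only in subscribers

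*Protocol article*

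**What the plan says.** **Survey first.** Study Design says that "a baseline survey will be conducted before recruitment to estimate the prevalence of SAD". Data Collection agrees: "A link to the baseline survey will be sent to the students through their email and WhatsApp", and all students, whatever their scores, "will have the option to enroll in the W4S program and will be made available through a postbaseline subscription link".

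**Subscription first.** Later in the same paragraph of Study Design: "All participants who subscribe to the intervention will receive a link to the online baseline survey, daily supportive messages for 6 months". Participants' Recruitment and Subscription has students register and consent, and then: "Once they have electronically consented to the study, they will receive another link to the baseline study". The abstract's Methods paragraph says: "The data will be collected from subscribers at baseline (program initiation), 1 month, 3 months (midpoint), and 6 months (program completion". Sample Size Estimation assumes that "a minimum of 4494 students will be enrolled in the W4S email and WhatsApp messaging program over 6 months to obtain an estimated 2247" students will complete the baseline.

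**Start of messages.** The section describing the W4S messaging intervention says: "Upon registration, they will receive daily supportive, noninteractive (one-way) messages for 6 months".

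**Use of the baseline.** Outcomes and Measures divides the number of likely cases by the number who completed the baseline survey. Statistical Analysis tests change with paired t tests and proportion tests across baseline, 1, 3 and 6 months. Study Design gives resource constraints as the reason for not randomizing.

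**The concern.** The two orders produce different data.

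- **Effectiveness (Objective 2).** With no control group, the baseline is the only comparator. If messages start at registration and the survey link arrives at or after registration, a student may answer after receiving messages. That score is not a pre-intervention value, and the change measured from it is not the full change since the programme began.
- **Prevalence (Objective 1).** The stated target is university students. If only subscribers get the survey link, the denominator is students who chose a mental-health support programme. Strengths and Limitations mentions other universities and low response, but not self-selection of subscribers within Makerere.

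A pre-message score that was not collected cannot be recovered later, so the order has to be settled before enrolment.

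**Working it through.** **1. The plan's own figures.** Inputs from Sample Size Estimation: population 35,000, expected prevalence 50%, 95% confidence, margin 2 points, completion 50%.

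- Without finite population correction: n0 = 1.96² × 0.5 × 0.5 / 0.02² = 2400.9.
- With correction: n = 2400.9 / (1 + 2399.9/35,000) = 2246.8, that is 2247. This reproduces.
- Enrolment: 2247 / 0.50 = 4494. This reproduces.
- Before-after sample of 90: reading the 30% effect size as a standardized paired difference of 0.30 (an assumption), a two-sided 5% paired t test has 80.4% power at n = 90. This reproduces.

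The arithmetic is sound. The question is which flow it describes.

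**2. Which flow the 4494 implies.** The 50% is applied to programme enrollees, so 4494 − 2247 = 2247 of them are expected to have no baseline. Enrolment in the programme therefore cannot depend on completing the survey. Under the flow in Data Collection, the 50% would apply to students invited to the survey, and programme enrolment would be a separate number that the protocol does not give.

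**3. The flows side by side.**

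| | Survey first | Subscription first |
|---|---|---|
| Where stated | Study Design (earlier sentence); Data Collection | Study Design (later sentence); abstract; recruitment section; sample size |
| Who gets the survey link | Students | Subscribers |
| First message relative to baseline | After, because subscription follows the survey | Not fixed; the intervention section says on registration |
| Prevalence denominator | All survey completers | Subscribers who complete the survey |

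The follow-up clock differs too: Study Design counts from enrolment, Midterm and Endline Evaluation from the start of messages.

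**4. Late baselines, illustration only.** Suppose that on average a fraction c of a 0.30 effect is already present at the recorded baseline. The measurable effect is 0.30 × (1 − c). The values of c are assumptions.

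| c | Measurable effect | Power at n = 90 |
|---|---|---|
| 0 | 0.300 | 80% |
| 10% | 0.270 | 72% |
| 25% | 0.225 | 56% |
| 50% | 0.150 | 29% |

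A larger achieved sample would restore power but not the understated effect.

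**5. Selection, illustration only.** If students with the condition are k times as likely to enter the sample, a true prevalence p is observed as pk / (pk + 1 − p). The values of k are assumptions.

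- p = 40%, k = 1.5: 0.60 / (0.60 + 0.60) = 50%.
- p = 40%, k = 2: 0.80 / (0.80 + 0.60) = 57%.
- p = 50%: k = 0.52 / 0.48 = 1.08 is enough to use up the 2-point margin.

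Here k combines selection by subscribing with selection by answering the survey. Only the first part depends on the order of steps.

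**The case against.** The strongest reply is that the protocol does contain sentences that put the baseline first. Followed literally, either the survey before recruitment or the post-baseline subscription link protects the baseline. The abstract equates baseline with programme initiation, the subscription-first sentences name the survey link before the messages, and the start on registration appears in a general description of the programme. Nowhere does the protocol say that the baseline follows the messages. This stands: a reader might infer that nothing in the plan requires a pre-message baseline, and that is too strong. The gap belongs to the subscription-first flow, and the defect is that both flows are in force.

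Registering for the study and enrolling in the programme might be separate steps. That does not resolve the conflict, because Study Design sends the baseline link to those who subscribe to the intervention and the sample size counts programme enrollees.

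Survey-first respondents are volunteers too. They learn of the intervention during the broadcast, and Strengths and Limitations expects response below 20%. This also stands: changing the order removes only the extra selection from requiring subscription.

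Enrollees without a baseline are missing pairs, not contaminated ones. A late baseline would not by itself create a false benefit. Finally, the study is a pilot for a randomized trial. That lowers the stakes, but prevalence and effectiveness remain its stated objectives.

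**Conclusion.** The contradiction is certain: it occurs within one paragraph of Study Design, and again between Data Collection and the recruitment and sample size sections. Under the subscription-first flow, two consequences follow. Some baselines can be taken after exposure, which biases the uncontrolled change towards a smaller improvement if the messages help. And the prevalence sample is confined to subscribers.

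Neither bias can be sized from the document, because it gives no number of late responders and no ratio of subscription rates by mental-health status. Two stronger inferences are not supported. One is that prevalence will be wrong by 10 to 17 points: the 40% read as 50% or 57% rests on assumed ratios that mix two kinds of selection, one of which remains under either order. The other is that half the baselines are contaminated: the 50% is a completion rate and says nothing about timing.

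**What to change.** State one sequence in the abstract, the intervention description, Study Design, Data Collection, the recruitment section and Sample Size Estimation. The preferable one is already in Data Collection: survey open to all invited eligible students, then the subscription link, then the first message. With it:

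- Use a baseline in the pre-post analysis only if its platform time stamp precedes the first message.
- Define the prevalence denominator as all survey completers, and report prevalence also by subscriber status.
- Apply the 50% completion rate to students invited to the survey, and state programme enrolment separately. At 50%, 2247 completers need 4494 invitations; at 20%, the ceiling that Strengths and Limitations gives for typical web surveys, they need 2247 / 0.20 = 11,235.
- Align the consent wording, which is tied to subscription or registration in some places and to clicking the survey link or submitting the survey in others.

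If subscription first is kept, hold messages until the baseline is complete and describe the prevalence as that among subscribers.

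Weighting by college and year of study is optional. It would not correct selection on SAD itself, and the protocol does not mention the registry totals it would need.

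**Cost:** a change in link order on the platform, one time-stamp check and revised consent text. Some survey completers will not subscribe, so the programme may enrol fewer students than it surveys.

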### Study Setting

The study will be conducted among Makerere University undergraduate students. The university has a population of over 35,000 students [44]. Since the baseline survey and the follow-up will be conducted virtually, general assumptions are made that all students own smartphones, have an email and WhatsApp, and can access free Wi-Fi at Makerere University.

### The Intervention: Cocreation of Email and WhatsApp Messages

For this protocol, the intervention to be delivered to the students at Makerere University is the ResilienceNHope program. The ResilienceNHope suite of interventions delivers daily supportive messages, often accompanied by images and links to mental health literacy resources, to its subscribers. A total of 15 students (8 female and 7 male) were selected across years of study (year 1, year 2, and year 3) at the College of Business and Management Sciences, Makerere University, to ensure representativeness of the cocreation team and to avoid potential biases in the adaptation process.

Supportive text messaging programs based on CBT principles, such as the W4S program within the ResilienceNHope suite, are among the most highly recommended digital interventions for SAD and have been successfully implemented in both Canada and Zambia [33-35,43]. The study team, together with selected undergraduate students and identified stakeholders, will adapt the W4S program, specifically tailoring messages and images to the Ugandan undergraduate university students’ population [43].

There are several adaptation frameworks. These include the ADAPT-ITT (Assessment, Decision, Adaptation, Production, Topical experts, Integration, Training, Testing), intervention mapping (IM) framework, and framework for reporting adaptations and modifications to evidence (FRAME), among others [38,45,46]. For this study, we will adapt the W4S program [33,43] using the IM adaptation framework [47]. The IM adaptation framework has 6 steps. First, establish a detailed understanding of the health problem, the population at risk, the behavioral and environmental causes, and the determinants of these behavioral and environmental conditions and assess available resources. Second, describe the behavioral and environmental outcomes, create objectives for changes in the determinants of behavior and environmental causes, and specify the targets of the intervention program. Third, identify theory- and evidence-based behavior change methods that influence the determinants and translate these to practical applications that fit the intervention context. Fourth, combine the intervention components into a coherent program that uses delivery channels that fit the context. Fifth, develop implementation strategies to facilitate the adoption, implementation, and maintenance of the program. Finally, plan both process and outcome evaluation to assess program implementation, efficacy, or effectiveness [47].

The adaptation is expected to improve the feasibility and acceptability of the W4S intervention [33-35,43]. The cocreation and adaptation will be done when students are in the recess term period (between June and July).

### Data Collection

An online baseline survey will be conducted to assess the mental health of the students.

A link to the baseline survey will be sent to the students through their email and WhatsApp. Clicking on the link to the baseline survey will indicate consent required for participation in the survey. The data collection portal is secure and password-protected with dual authentication, which minimizes data breaches. In addition to the demographic questions, participants will fill out the online screening tools for assessing SAD and well-being. It is on this basis that they will be diagnosed (to have or not to have) with at least one of the 3 outcomes [8,48-50]. The app is programmed to produce summaries of the total number of subscribers at any given point in time and how many have completed the different phases.

All participants will be able to view their scores for each mental health outcome (SAD). Depending on the severity of the mental health scores, recommendations will be provided to participants. All students, whether diagnosed with SAD or not, will have the option to enroll in the W4S program and will be made available through a postbaseline subscription link. The baseline survey and intervention enrollment will be conducted from March 2026 to cover the second semester of the academic year 2025/2026 at Makerere University.

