### Baseline Survey

A structured baseline survey questionnaire will be developed to measure students’ mental health outcomes. The questionnaire will include the 10-item Perceived Stress Scale (PSS-10), 7-item Generalized Anxiety Disorder (GAD-7) scale, 9-item Patient Health Questionnaire-9 (PHQ-9) scale, and WHO-5 (World Health Organization-Five Well-Being Index) scale to measure SAD and well-being [20,49,51-53]. These tools have been validated for making comparisons between population subgroups [35]. The questionnaire will also include sociodemographic and economic variables, including age, relationship status, religion, orphanhood status [54], college, sponsorship status, working status, living arrangement, year of study, and current academic performance among others. Participant data will be collected online through self-administered questionnaires on the ResilienceNHope platform [43]. The data will be hosted online on the ResilienceNHope server and downloaded for analysis.

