### Follow-Up Surveys

A follow-up survey questionnaire will be used to assess improvements in the students’ mental well-being using validated scales for SAD, using the PSS-10, GAD-7, and PHQ-9. These surveys will be conducted at 1 month, 3 months (mid-term evaluation), and 6 months of the study (endline evaluation). The app has automated email reminders at 6 weeks, 3 months, and 6 months to boost completion rates. In addition, receiving daily messages with images is an incentive to students, and this was tested during the cocreation process with students.

The questionnaire will also include variables on participants’ satisfaction with the W4S program intervention and suggested improvements and recommendations. Participant data will be collected and hosted online through self-administered questionnaires on the ResilienceNHope web platform [43] and downloaded for analysis. We recognize that retention is and has been a challenge for online surveys; part of the mitigation strategy is to make the survey shorter. The number of questions was reduced to the bare minimum.

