### Ethical Considerations

Ethical approval for this study was granted by the AIDS Support Organisation Research Ethics Committee (TASO-2025‐2141) and the Uganda National Council of Science and Technology (UNCST SS4200ES).

Participation in the study will be voluntary, where students will self-subscribe to receive daily supportive emails and WhatsApp messages for 6 months. All respondents will be assured of confidentiality, and participants will be made aware that informed consent will be implied when they complete and submit the survey. Privacy and confidentiality will be guaranteed. The data will be anonymized and deidentified, and protective measures will be taken to safeguard participant information. All students will be compensated with a one-off airtime compensation of CAD $5 (equivalent to US $3) after completing the surveys.

Potential participants will be informed of their right to withdraw from the study. The online questionnaire will automatically end upon their declining to participate in the study. The dataset from the website is programmed to be downloaded without identification particulars (deidentified), and therefore, no personal information will be publicized. The particulars of the respondents are only available to the principal investigator and the core research team.

Students with adverse mental health outcomes will be referred to the university’s Counselling and Guidance Center or advised to seek professional help.

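### Recommendations follow score severity, so a student who endorses the PHQ-9 self-harm item but has a low total would be handled as low severity; an item-level check would close this cheaply

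*Protocol article*

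**What the plan says.** Under Data Collection, students complete online screening tools for stress, anxiety and depression (SAD) and well-being, and on that basis "they will be diagnosed (to have or not to have) with at least one of the 3 outcomes". Feedback follows: "All participants will be able to view their scores for each mental health outcome (SAD"), and then "Depending on the severity of the mental health scores, recommendations will be provided to participants". No cut-off is printed, and the content of the recommendations at each severity level is not described.

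The depression tool at baseline is the "9-item Patient Health Questionnaire-9 (PHQ-9) scale" (Baseline Survey). The follow-up questionnaire at 1, 3 and 6 months measures the same conditions "using validated scales for SAD, using the PSS-10, GAD-7, and PHQ-9" (Follow-Up Surveys). All surveys are self-administered on the web platform.

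Ethical Considerations adds a second route: "Students with adverse mental health outcomes will be referred" to the university's counselling service or advised to seek professional help. The term that triggers this is not defined. The same section says: "The particulars of the respondents are only available to the principal investigator and the core research team".

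The intervention itself does not receive replies. On registration, "they will receive daily supportive, noninteractive (one-way) messages for 6 months".

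**The concern.** The total score and the self-harm item answer different questions. The total measures how heavy the depressive symptoms are. The item records a disclosure that calls for a prompt response whatever the total. A feedback rule driven by severity reads the first and can pass over the second.

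This matters more than usual here because of how the study makes contact. The surveys are completed alone and online, and the messages run one way, so among the contacts the article describes, the survey is where a student would disclose such thoughts. The principal investigator and core team can identify respondents, so someone could act later on an individual answer, but the article does not say who would do so or when. The immediate response is the on-screen recommendation, and its stated basis is score severity.

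**Working it through.** The plan gives no figure on this point to reproduce. The check is whether an endorsed self-harm item can coexist with a low score, and whether any other stated rule clearly catches it.

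**Inputs**
- From the protocol article: the nine-item PHQ-9 at baseline and the PHQ-9 at three follow-ups; recommendations by score severity; no printed cut-off.
- Assumed (standard instrument content and scoring, not in the article): one of the nine items concerns self-harm; each item scores 0 to 3; the score used for feedback is the scale total.
- Assumed cut-offs, because none is given: 5, 10 and 15.

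**Step 1: range of the scale.** Maximum total = 9 × 3 = 27. Maximum of the other eight items = 8 × 3 = 24.

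**Step 2: only the self-harm item endorsed.** The total equals the item score: 1, 2 or 3 of 27. Even the most frequent response leaves the student at the bottom of the scale.

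**Step 3: room left below a cut-off.** Let C be the cut-off and s the self-harm item score. The total stays below C when the other eight items sum to at most C − 1 − s.

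| Cut-off C | Item score s | Largest sum of the other eight items |
|---|---|---|
| 5 | 3 | 5 − 1 − 3 = 1 |
| 10 | 3 | 10 − 1 − 3 = 6 |
| 15 | 3 | 15 − 1 − 3 = 11 |
| 10 | 1 | 10 − 1 − 1 = 8 |

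At C = 10 with the item at its maximum, the totals concerned run from 3 to 9. At C = 5 the window is narrow; at C = 15 it is wide.

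**Step 4: occasions.** 1 baseline + 3 follow-ups = 4 possible submissions per student.

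**Step 5: the other stated rules.**
- *Referral (Ethical Considerations).* It depends on an undefined term. Data Collection uses the word outcomes for the three screened conditions, so the trigger can be read as a scale result. It can equally be read in its plain sense, which would include thoughts of self-harm. The text does not settle this.
- *Daily messages.* They are one-way and cannot respond to a survey answer.
- *Data quality checks (Data Quality Assurance).* They concern consistency and accuracy of uploaded data, not participant safety.

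No section of the article describes a check on a single item.

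**The case against.** The strongest reply is that this is a journal article summarising a longer protocol. Data Collection does not use the word total, does not say that severity is the only trigger, and does not say what low scorers are told; counselling contacts might be shown to everyone. Item-level alerts and crisis screens are the kind of operational detail a full protocol or ethics file would hold, and the study has approval from a research ethics committee and the national council. The referral sentence is not tied to a cut-off or a survey wave.

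Much of that stands, and it rules out several stronger readings.

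- A reader might infer that the study has no procedure for suicide risk. The article cannot show this; a procedure may exist elsewhere or already be built into the app.
- A reader might infer that referral excludes self-harm thoughts. The text is silent on them and does not exclude them, and an undefined term in a condensed article is missing detail, not an error.
- A reader might infer that the follow-ups are uncovered, because Follow-Up Surveys mentions neither score viewing nor recommendations. The referral sentence is not limited to baseline, so that silence does not show a gap.
- A reader might multiply the 2247 planned baseline completers by an assumed rate to obtain a count of affected students. The article gives no rate, so the count would only restate the assumption.

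What the reply does not remove is that the one feedback rule the article does state depends on score severity, and that such a rule, applied as worded, can miss this answer.

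**Conclusion.** The point holds as a limited design improvement. The stated basis for on-screen recommendations is the severity of the scale scores, and on standard PHQ-9 content and scoring that basis can place a student with the strongest possible self-harm response in a low band: below 10 of 27 whenever the other eight items sum to 6 or less. The referral route may catch the student, but the article does not say that it does.

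The conclusion rests on three assumptions: that the PHQ-9 is used in its standard form, that feedback reads the scale total, and that no item-level rule already sits in documents not shown. The frequency of the pattern is unknown. No sample size, power or analysis result is affected. The case for change is that a rule which reads the item is safer than one which reads only the score, and it costs little.

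**What to change.** In Data Collection, state that the platform checks the self-harm item separately from the total at every PHQ-9 submission: baseline, 1, 3 and 6 months. For any non-zero answer, whatever the total, it should immediately display counselling or crisis contacts together with the advice to seek professional help that Ethical Considerations already foresees. If enrolment has begun, the rule can apply from the next submission.

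The cost is one item-level condition and one contact screen in an app that the Abstract (Results) reports as complete, so it would have to be reopened. Feedback may also have to be added at three follow-ups where none is described. The screen needs no new question and no extra staff. It may prompt some more self-referrals to a service that the Introduction describes as scarce, with counsellor ratios often beyond 1 to 10,000 students.

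Active referral of every non-zero answer, or an alert linked to the student's identity, is a different matter. It would add load to that service and raises confidentiality questions, so it should be left to the sponsor's clinicians and the ethics committee. If an equivalent procedure already exists in the full protocol, one sentence in the article pointing to it would be enough.
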